#### Randomisation and allocation concealment

After consent each participant is randomly allocated to the intervention or control group, facilitated by a computerised centralised allocation process which forms part of the online registration procedure. Eligible healthcare consumers are randomly assigned to the intervention or control group using a computer generated random number sequence in randomly assigned blocks (block sizes 2, 4 and 8) with intervention allocation ratio of 1:1 [32].

The randomisation sequence generation, participant registration, and group allocation processes are computerised online and do not involve human interventions from the investigators. The block randomisation sequence is pre-generated by a member external to the research team using a computerised random-number generator before commencing participant recruitment. As each participant completes the online registration procedure, he/she receives the next consecutive allocation in the sequence, which automatically assigns the consumer to the intervention or control group.

#### Blinding and assessment

Since *Healthy.me *is a behavioural intervention it is not possible to completely blind participants to the intervention. The group allocation is revealed to participants only after obtaining their consent to participate in the study and completion of the pre-study survey. However, investigators and clinicians involved in the study are blinded to group allocation. To minimise contamination of control participants who might interact with participants who are part of the intervention group, participants in the intervention group are asked not to share their *Healthy.me *access details with other people. Further, participants who self-reported to have been influenced by others participating in the study to obtain (or not obtain) influenza vaccination will be excluded from analysis. To assess the success of blinding, administrative staff at the University Health Service will be consulted at study completion to confirm whether clinicians involved in assessing patient outcomes and/or administrating influenza vaccination are able to distinguish patients who booked an appointment using *Healthy.me*.

## Discussion

Health promotion and surveillance have received unprecedented recognition because of newly emerging and re-emerging infectious diseases with epidemic potential, new cycles of pandemics, and the threats of bioterrorism. Influenza and influenza-like illness (ILI) are important contributors to population and individual morbidity and mortality. The recent influenza pandemic with novel H1N1 has highlighted the need for a better understanding of patients' healthcare seeking behaviour and perceptions and attitudes towards vaccination. Findings of our study will help to facilitate health promotion and surveillance in technology savvy populations as well as to enhance healthcare professionals' and governments' capacity to predict and prepare for the subsequent epidemics and pandemics.

The study will further explore the role of clinical illness case definitions for influenza as methods used to define influenza seasons have varied substantially. These differences often result in differing levels of sensitivity, specificity and positive predictive value for the case definitions used. Furthermore, these differences affect the estimation of influenza vaccine effectiveness, safety and cost benefit analyses in healthy working adults [24,33].

## Limitations

There are several potential limitations in this study:

• *Number of eligible participants*: Recruitment may be affected by an overlap between the start of respiratory season in Australia and the student examination period, potentially affecting student and staff availability and interest to participate in research studies. The number of participants meeting exclusion criteria at study completion might be significant because staff members are eligible for free influenza vaccination offered by UNSW one week prior to study commencement. As free vaccination would be a confounder if included in this trial, we explicitly ran our campaign independently of the university program.

• *Self-reports of influenza vaccination and health service utilisation*: Since clinical audits will only be conducted at the University Health Service, and not other GP practices, the study is dependent on participants' self-reporting of their influenza vaccination and health service utilisation. Self report has shown to be acceptably accurate in numerous studies examining days of absence [34], influenza symptoms, and vaccination status for diverse patient cohorts [20,33,35-38]. We will minimise the risk of recall bias by conducting short one-minute monthly follow-up surveys on the first week of each month.

• *Representative of general healthcare consumers*: The study may be more appealing to consumers who are interested or literate in computers, the Internet, or health-related topics. These participants may be more enthusiastic about health and the Internet than the general health consumer population. In addition, participants from a university setting are more likely to be open and positive to new research ideas and willing to participate in research studies. Further, generalisability of findings could be limited by recruiting participants from one university.

• *Social influence and access to Healthy.me*: The social networks of individual participants may span the intervention and control arms of this study, and see intervention subjects un-blind control subjects with information obtained from the intervention. As this is a pragmatic trial in the real world, such effects cannot be controlled for. Indeed participants' social networks are likely to influence access to Healthy.me if the intervention was in routine use. We will attempt to measure this effect by asking participants in the control arm if they have been in contact with intervention arm subjects. If a significant group is identified, we will conduct separate analyses to estimate the impact of any such effect on overall trial results.

• *Baseline comparisons*: As this is a pragmatic trial of a multifaceted intervention in a complex environment, it is possible that baseline variables associated with subjects might also influence the outcome. For example, having a prior history of obtaining influenza vaccination may predict future vaccination rates, independently of any additional intervention. We will identify potential baseline variables that might influence outcome, including gender, and test for unequal distribution of these variables in the intervention and control populations. Should there be a significant difference in their distribution due to chance bias, these will be fitted in an analysis of covariance to model their impact on any observed differences between the two arms [39].

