### Participants and setting

Table 1 outlines participant inclusion and exclusion criteria. The study will recruit students and staff members at UNSW who are fluent in English. Written material advertising the study outlines participant inclusion criteria, which are self-explanatory (i.e. age ≥ 18 and monthly access to Internet and email). Exclusion criteria are applied post-study. Hence, participants who self-identify as meeting inclusion criteria proceed to first providing informed consent before commencing the pre-study survey.

**Table 1 T1:** Eligibility criteria for participants

Inclusion criteria	Exclusion criteria
1. Aged 18 or above.	1. Participants who did not complete registration process [excluded before randomization].

1. Access to the Internet, and email at least on a monthly basis.	2. Participants who self-reported having obtained an influenza vaccination in 2010 prior to enrolment in the study [excluded from analysis].

	3. Participants who self-reported to be influenced by other participants during the study to obtain (or not obtain) influenza vaccination [excluded from analysis].

Participants engage in this trial online in their own space at their own time. All participants are required to complete online (i) a 5-10 minute pre-study survey; (ii) a monthly one-minute survey to collect their health symptoms and health service use; and (iii) a 5-10 minute post-study survey. Participants allocated to the *Healthy.me *group are also required to complete a five-minute mandatory online tutorial about system before commencing the study. Those who complete all study surveys will enter into a draw for $500 prize at study completion.

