### Sample size considerations

The sampling unit is the participant and the unit of analysis is also the participant. A conservative estimate of 600 participants with 300 in each group is needed to detect a 10% difference in influenza vaccination rate between the control group (15%) and the intervention group (25%). This estimate is calculated at 5% level of significance, 80% power (two-sided test), with an anticipated participant dropout rate around 10% [12].

The effect size estimate is based on a review assessing the effectiveness of patient reminder systems in improving immunization rates, which can range from 5 to 20% [13]. The baseline rate estimate of influenza vaccination was informed by our audit conducted at the University Health Service, showing 16% of patients at the practice received FluVax or PanVax between 5/3/2009 to 5/11/2009. This estimate is also supported by literature reporting 18 to 30% of university students and healthy adults (18 to 49 years old) obtaining influenza vaccination in a year [14,15].

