### Analysis plan

Statistical significance is defined a priori as a P value of less than 0.05 (determined using a two-tailed test). Data will be collected by online survey software KeySurvey [27] and analysed using PASW Statistics 18 [28].

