#### Baseline comparisons

Comparisons of baseline variables between PCHMS and waitlist groups will be conducted using Student's t-tests for continuous variables and χ^2 ^tests for categorical variables, to assess whether randomisation was performed properly. Adjustment for baseline characteristics is planned to correct for possible imbalance between the randomised groups and to provide a stratified estimate of the effect of intervention if applied [29,30].

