#### Primary analysis

Differences in proportions of participants obtaining influenza vaccination during the study will be compared between waitlist and PCHMS groups. All intervention recipients who had the opportunity to use the PCHMS but did not do so will be included in the primary analysis. Differences in participant proportions between waitlist and PCHMS groups will be analysed using χ^2 ^test. Proportions will be reported with 95% confidence intervals.

Adjustments for baseline characteristics and potential confounders will be made through the use of sequential logistic regression [31]. Baseline characteristics (Table 1), and factors that may affect influenza vaccination collected at post study (i.e. contact with children during study, past history of influenza vaccine) will be entered at Step 1 of the regression; and group allocation (PCHMS vs. waitlist) will be entered at Step 2.

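### The Primary analysis and Limitations sections give conflicting rules for covariate adjustment of the yes/no primary outcome, and one of them is triggered by baseline significance tests

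*Protocol article*

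**What the plan says.** Four places in the protocol article bear on the point.

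- **Analysis plan, Primary analysis.** The proportions vaccinated are compared by a chi-square test and reported with 95% confidence intervals. The next paragraph, under the same heading, states: "Adjustments for baseline characteristics and potential confounders will be made through the use of sequential logistic regression". No condition is attached. Step 1 takes the covariates, introduced as "Baseline characteristics (Table 1", together with two factors collected at the end of the study: contact with children during it, and past influenza vaccination. Group enters at Step 2.
- **Participants and setting, Table 1.** The table cited for the baseline characteristics is titled "Eligibility criteria for participants".
- **Analysis plan, Baseline comparisons.** t-tests and chi-square tests compare the arms at baseline "to assess whether randomisation was performed properly". Adjustment for possible imbalance is planned; no model and no trigger is named.
- **Limitations, bullet on baseline comparisons.** Variables that might influence outcome, gender among them, will be identified and tested between arms. Then: "Should there be a significant difference in their distribution due to chance bias, these will be fitted in an analysis of covariance". The example given is a history of vaccination predicting later vaccination, so the bullet is about the primary outcome.

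**The concern.** The Primary analysis and the Limitations bullet differ both on when to adjust (always, or only after a significant baseline test) and on the model (logistic regression, or analysis of covariance). An analyst cannot comply with both.

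The trigger is also unsound. The Randomisation section describes a sequence generated in advance by someone outside the team and applied by computer. Differences between the groups as randomised are then chance, as the bullet itself says. A p-value for such a difference does not show whether randomisation was done properly, and it does not show which covariates matter. That depends on how strongly a variable predicts vaccination.

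At stake is whether the adjusted result is fixed in advance. With two rules, a covariate reference that leads to the wrong table, and no statement of which analysis decides, more than one p-value could be put forward as the primary result.

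**Working it through.** **1. Inputs from the article.** Significance level, from Analysis plan: "Statistical significance is defined a priori as a P value of less than 0.05 (determined using a two-tailed test". Design, from Sample size considerations: "This estimate is calculated at 5% level of significance, 80% power (two-sided test", for a "10% difference in influenza vaccination rate between the control group (15%) and the intervention group (25" per cent, with about 10% dropout and 300 per group.

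**2. The plan's own figure.** Pooled rate (0.15 + 0.25)/2 = 0.20.

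- Uncorrected: n = [1.96·√(2·0.20·0.80) + 0.842·√(0.15·0.85 + 0.25·0.75)]² / 0.10² = (1.109 + 0.472)² / 0.01 ≈ 250 per arm.
- With continuity correction: (n/4)·[1 + √(1 + 4/(n·0.10))]² = 62.5·(1 + √1.16)² ≈ 270 per arm.
- After dropout: 270/(1 − 0.10) = 300 per arm, 600 in total.

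The stated 600 is reproduced exactly by an unadjusted comparison of two proportions. The adjustment conflict does not change it.

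**3. The two rules side by side.**

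| | Primary analysis | Limitations bullet |
|---|---|---|
| When adjusted | Always | Only if a baseline test is significant |
| Model | Sequential logistic regression | Analysis of covariance |
| Covariates | Table 1 (eligibility criteria) plus two post-study factors | To be identified; gender named, prior vaccination as an example |

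**4. How often chance fires the trigger.** For k independent tests at 5%, P(at least one significant) = 1 − 0.95^k. The article gives no count, so k is an assumption.

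- k = 3: 14%
- k = 5: 23%
- k = 8: 34%
- k = 10: 40%

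**5. Error rate if the analyses compete.** Simulation with no treatment effect: 270 per arm, 15% vaccinated, 4,000 runs per setting. Five binary covariates were assumed, one with 30% prevalence and four with 50%. The analyses were an uncorrected chi-square test, a logistic model with all five covariates, and a linear model with only those covariates whose baseline test was significant.

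| Assumed log-odds (first covariate; others) | Chi-square | Logistic | Triggered linear | Any of the three |
|---|---|---|---|---|
| 1.0; 0.3 | 5.1% | 5.5% | 5.2% | 6.4% |
| 2.0; 0.5 | 5.6% | 5.6% | 5.3% | 7.7% |
| 3.0; 0.5 | 5.1% | 4.6% | 4.5% | 7.4% |

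The Monte Carlo standard error of the last column is about 0.4 percentage points. Each analysis alone stays near 5%; the excess comes from being able to choose. The further freedom of an open covariate list was not simulated.

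**The case against.** The strongest reply is that the article already has a natural reading: chi-square first, as the primary test, and logistic regression second, as the adjusted analysis. The chi-square test is named first and agrees with the sample-size calculation, and a ranking of the two is often left to the SAP, which is not shown. This carries weight. It is why the deciding analysis needs only a clarifying sentence, and why the text does not show that the trial has no primary test. It does not remove the conflict between the two adjustment rules, which are both stated commitments.

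Several stronger readings are tempting, and the documents do not support them.

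- **Three incompatible rules.** The Baseline comparisons section names neither model nor trigger and can be read together with the Primary analysis. The firm conflict is between two places.
- **Prior vaccination would go unadjusted.** The Primary analysis enters past influenza vaccination at Step 1 whatever any test shows.
- **Power would be gained by the fix.** Simulation with one strong assumed covariate (log-odds 1.8, prevalence 30%, 270 per arm, 15% against 25%) gave 83% power unadjusted and 88% adjusted. Unconditional adjustment is already planned, so that difference is not a gain from this correction.
- **23% or 40% as a false-positive rate.** These are chances that the trigger fires. Adjusting because of a chance imbalance did not by itself raise the error in the simulation.
- **Analysis of covariance as invalid in itself.** The linear model held its error near 5%. The objection is that it conflicts with the logistic model already named for this outcome, and estimates a difference in proportions where the other gives an odds ratio.
- **No covariates named at all.** Two factors appear under Primary analysis, and gender and prior vaccination in the bullet. The Table 1 reference may be a numbering slip, but as printed it does not identify the baseline set.

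**Conclusion.** The concern holds in a limited form. The article states two adjustment rules for the same binary outcome that cannot both be followed, and one rests on a significance trigger with no sound basis under computerised allocation. The table cited for the covariates is the wrong one, and the deciding analysis is implied rather than stated. These are things the document says wrongly, not detail left to an SAP.

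The size is modest: about 6.4–7.7% in place of 5% if any significant result among the three analyses were accepted, under assumed covariate numbers and strengths. The trigger probabilities rest on an assumed number of independent tests. The statement that baseline differences are chance applies to the groups as randomised. After the post-study exclusions, differences could have other causes, but a baseline test would still not show whether randomisation was performed properly. The correction should be made before outcome data are analysed; the trial's validity does not turn on it.

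**What to change.** - **Primary analysis:** state that the chi-square test decides, as it matches the sample-size calculation, and that one logistic model is the supportive adjusted analysis. The reverse is acceptable if stated in advance.
- **Covariates:** always include a fixed list measured before randomisation, for example prior influenza vaccination, gender, age and staff/student status. Contact with children during the study does not belong in that list. Correct the Table 1 reference to point to it.
- **Limitations bullet:** delete the significance trigger and the analysis of covariance, and refer to the logistic model instead.
- **Baseline comparisons:** describe the arms at baseline, and drop the use of tests to judge the randomisation.

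The cost is wording, plus collecting prior vaccination at registration if the pre-study survey does not already ask for it. The sample size stays at 600.

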### Concluding remarks

Our design of this randomised controlled trial (RCT) focuses on the comparison of outcomes that unequivocally reflect a change in consumer behaviour, and takes into account the complexity of intervention. Results of this study will offer new insights about the utility of online social networking for public health and health promotion. Our findings will provide specific answers to whether using a web-based PHCMS, with connectivity to a health service provider, containing information and self-management tools that facilitate consumers to act on a decision, will improve the uptake of preventive health services amongst students and staff in a university setting.
